#### **6.4 Summary of known and potential risks and benefits**

The intended benefit of study drugs is to reduce the severity of hand eczema.

Main risks in the *alitretinoin* group are (10):

- Teratogenicity of the study drugs
- Occurrence of allergic / anaphylactic reactions
- Depression with anxiety, mood changes and suicidal tendencies
- Sunburn
- Xerostomia, xerosis cutis
- Keratoconjunctivitis sicca, keratitis, blurred (night) vision, cataract. Care must be taken when driving a vehicle or when operating machines
- Myalgia, artralgia, increase of CK values
- Exostosis, ankylosing spondylitis
- Headache
- Blushing
- Increase of cholesterol and triglycerides, with ultimately pancreatitis
- Decrease of TSH and T4
- Increased liver transaminases
- Decrease in effective dose of simvastatin
- Change at scarring or dermatitis during therapy and 6 months after in case of aggressive dermabrasion or epilation
- Anemia
- Epistaxis
- Alopecia
- Benign intracranial hypertension (rare and most seen in combination with tetracyclines)
- Inflammatory bowel disease (rare)
- Vasculitis (rare)

Main risks in the *azathioprine* group are (18):

- Occurrence of allergic / anaphylactic reactions
- (Severe) myelumsuppression (this can occur independent of TPMT activity)
- Hepatotoxicity

- Nausea
- Exacerbation of a varicella zoster virus infection
- Inhibition of anticoagulation effect of coumarines
- Possibly teratogenic
- Increased sensitivity to infections (viral, fungal, bacterial)
- Alopecia (rare)
- Progressive multifocal leucoencephalopathy (rare)
- Development of non-Hodgkin lymphoma, non-melanoma skin cancer, sarcoma and cervix carcinoma, related to duration of treatment with immunosuppressant (rare)
- Stevens-Johnson, toxic epidermal necrosis (rare)
- Reversible pneumonitis (rare)

### 6.5 Description and justification of route of administration and dosage

Group I will receive an oral *alitretinoin* capsule of 30mg once daily for a total of 24 weeks. In a dose-finding study, the effectiveness and tolerability of this dose was established and it is recommended to use this as the standard dose for the prescription of alitretinoin in hand eczema. (8,10)

Group II will receive oral *azathioprine* tablets twice daily in a dose of 1.5 or 2.5mg/kg/day, depending on the thiopurine methyltransferase (TPMT) activity. A blood sample to measure TPMT activity will be obtained at the randomization visit. In thiopurine metabolism, the activity of the gene that encodes for the expression of the TPMT enzyme has an important effect on the toxicity of thiopurines in the human body. Genetic interpersonal differences lead to a difference in TPMT activity. Patients with low or absent activity of TPMT (0.3% of patients) have a risk of fatal myelosuppression when given normal doses of thiopurines. The result of the test is available in 3-4 weeks in our center. Patients will be allowed to continue their current topical treatment (if this is in accordance with the in-/exclusion criteria) for three more weeks and are required to taper the strength of topical corticosteroids to maximum class 2 during the week prior to baseline. At the azathioprine baseline visit (4 weeks following randomization visit) patients receive a dosage of azathioprine tailored to their TPMT activity. Patient with a low or absent TPMT activity (indicating homozygous or compound heterozygous mutations) will be excluded from the study. Patients with intermediate activity of TPMT (indicating heterozygous mutation) will receive 1.5mg/kg/day. Dosage in patients with normal to high activity levels of TPMT (indicating homozygous wild-type) will receive 2.5mg/kg/day. This is in accordance with current guidelines. (20)

## **6.6 Dosages, dosage modifications and method of administration**

The study drugs will be distributed to participants in amounts that allow drug intake as per protocol up to the next visit, 4 weeks later.

Dosage reduction is allowed in both groups in case of abnormal findings on physical examination, laboratory markers, and/or adverse events. Alitretinoin dose can be reduced from 30mg/day to 10mg/day, in accordance with the SPC-text.

*Alitretinoin* capsules need to be administered orally once daily, during a meal.

*Azathioprine* tablets need to be administered orally with a glass of liquid (200ml), during a meal.

## **6.7 Preparation and labelling of Investigational Medicinal Product**

Preparation and labelling of the study drugs will be carried out according to usual practice by the community pharmacy, honouring relevant GMP guidelines.

## **6.8 Drug accountability**

Not applicable.

## **7. NON-INVESTIGATIONAL PRODUCT**

Not applicable.

- 7.1 Name and description of non-investigational products**
- 7.2 Summary of findings from non-clinical studies**
- 7.3 Summary of findings from clinical studies**
- 7.4 Summary of known and potential risks and benefits**
- 7.5 Description and justification of route of administration and dosage**
- 7.6 Dosages, dosage modifications and method of administration**
- 7.7 Preparation and labelling of Non Investigational Medicinal Product**
- 7.8 Drug accountability**

## 8. METHODS

### 8.1 Study parameters/endpoints

#### 8.1.1 Main study parameter/endpoint

##### *Severity of hand eczema*

The Physician Global Assessment (PGA) developed by Ruzicka et al, covers 5 degrees of severity (clear, almost clear, mild, moderate, severe) and takes into account the intensity and percentage of hand surface involved. (8,9) Response to treatment is defined as an improvement of  $\geq 2$  steps on the PGA. Severe hand eczema is defined as responding to treatment if a status of at least 'mild' is achieved. Moderate hand eczema is defined as responding to treatment if a status of at least 'almost clear' is achieved.

In this study the main endpoint is the between-group difference in response to treatment between baseline and 24 weeks of treatment.

#### 8.1.2 Secondary study parameters/endpoints

##### *Severity of hand eczema*

- Between-group difference in mean change in PGA between baseline and 12 and 24 weeks.
- Between-group difference in response to treatment between baseline and 12 weeks of treatment.
- Between-group difference in mean change between baseline and week 4, 8, 12 and 24, assessed by the Hand Eczema Severity Index (HECSI) score. (21) The HECSI is an objective severity assessment based on clinical symptoms only. It includes erythema, fissures, vesicles, scaling, oedema, papules and measurement of the affected area. The score ranges from 0-360, with 360 indicating the most severe eczema.
- Between-group difference in time to response (time to first PGA improvement of  $\geq 2$  steps). This is only measured at control visits so possible outcome is limited to 4, 8, 12 and 24 weeks.

##### *Patient rated outcome measures (PROMs)*

##### *Quality of life*

- Between-group mean change in quality of life between baseline and 12 and 24 weeks, assessed by the Quality Of Life in Hand Eczema Questionnaire (QOLHEQ). The QOLHEQ is a multi domain disease specific instrument for

hand eczema assessing impairments in quality of life. The score ranges from 0-120, with 120 indicating worst quality of life.

*Patient reported improvement*

- Between-group difference in patients reporting improvement as 'clear or almost clear' at week 12 and 24, assessed by Patient Global Assessment (PaGA). The PaGA takes signs and symptoms into account. It covers 6 degrees of improvement: 'clear or almost clear' (at least 90% clearing of disease signs and symptoms compared to baseline), 'marked improvement' (at least 75% clearing), 'moderate improvement' (at least 50% clearing), 'mild improvement' (at least 25% clearing), 'no change', or 'worsening'. (9)

*Safety and tolerability*

- Adverse events in both groups will be registered.

*Cost-utility and cost-effectiveness*

- Between-group difference in mean Quality Adjusted Life Years (QALY's) will be measured by the EQ-5D-5L score at baseline, week 12 and week 24. The EQ-5D-5L is a measure for HRQoL and utility values. The EQ-5D-5L questionnaire includes a descriptive system, which comprises 5 dimensions of health: mobility, self-care, usual activities, pain/discomfort, and anxiety/depression. Moreover it includes a visual analog scale (VAS), which records the respondent's self-rated health status on a graduated (0–100) scale.
- Direct medical costs will be determined using standardized prices for consultation, treatment (medication; alitretinoin or azathioprine, topical treatment of corticosteroids and emollientia; if necessary oral or topical treatment of antibiotics), diagnostic tests, laboratory measurements, visits to the general practitioner for hand eczema and hospital admissions (in patient and/or daycare). Included patients will be asked to keep track of how much they spend on over-the-counter medication and other products for their hand eczema (out-of-pocket costs). Direct non-medical costs, consisting of travel costs, will be determined using average travel costs to the hospital as determined by relevant Dutch guidelines on cost-studies in healthcare. (22)
- Indirect costs, consisting mainly of productivity loss, will be also be calculated using tables from the guidelines with average income of Dutch workers stratified by age and gender, corrected for shift working / irregular working hours.

### 8.1.3 Other study parameters

At baseline age, sex, Body-Mass-Index, current and history of atopic dermatitis (both defined by U.K. Working Party criteria) (23), age of onset of atopic dermatitis, age of onset of hand eczema, current use of statins, current use of thyromimetics, currently smoking and amount of pack-years will be registered because these might be confounders. (2,24) Pack years are calculated by multiplying the total years smoked with the average packs per day smoked over these years. (25) For this, we use the online Smoking Pack Years Calculator, created by dr NJ Masters and C Tutt. (26)

## 8.2 Randomisation, blinding and treatment allocation

Randomization is carried out by a computer program.

This is a study with blinded efficacy assessors, which are unaware of treatment allocation. The participants and treating physician will be aware of treatment allocation. Efficacy assessment will be carried out by physicians or specialized eczema nurses who are experienced in assessing hand eczema by PGA and HECSI in daily practice. Blinding will only be broken after analyzing the data.

At screening visit (-1 week for *alitretinoin*, -5 weeks for *azathioprine*), clinical eligibility of patients is assessed. If eligible, patients are given a least 1 week time to consider participation in the study. If patients choose to participate they will be randomized to alitretinoin or azathioprine treatment (at week 0 for *alitretinoin*, -4 weeks for *azathioprine*). Based on the assigned group, appropriate laboratory assessments will be performed. If these assessments do not show abnormalities as described in the *laboratory exclusion criteria post randomization*, patients will receive the treatment.

## 8.3 Study procedures

Procedures part of standard medical treatment:

According to daily practice, a detailed patient history is obtained of all newly referred patients with hand eczema, and they are planned for patch testing to exclude contact allergy. During this first period, patients are treated with topical corticosteroids and emollients. Standard skin care advice is provided and exposure to provoking factors is discussed. If a relevant contact allergy is ruled out and the hand eczema proves to be refractory to topical therapy and/or UV therapy, the next step is systemic therapy. These patients are a candidate for the current study.

Laboratory analysis is performed to verify contra-indications for systemic treatment; in the current study alitretinoin or azathioprine. For azathioprine this check takes 4 weeks, due to the necessary measurement of TPMT (see paragraph 6.5). During therapy, standard

monitoring of blood values is carried out, according to SPC texts and current guidelines. At every visit, the Physician Global Assessment (PGA) for severity is determined (9) and the hand eczema is scored using the Hand Eczema Severity Index (HECSI, see appendix) (21), corresponding to our daily practice. Additionally, a Patient Global Assessment (PaGA) for improvement is obtained at week 12 and 24. Furthermore, health related quality of life is scored with a Dutch version of the Quality of Life in Hand Eczema Questionnaire (QOLHEQ, see appendix) at the start of therapy, at week 12 and week 24. (27)

Standard laboratory tests to be performed include:

*Alitretinoin*: at week 0, 4, 8, 12 and 24, laboratory tests are carried out, including: full blood count, ASAT, ALAT, ALP,  $\gamma$ -GT, serum creatinine, cholesterol, triglycerides, HDL, TSH, T4, glucose. At baseline, a pregnancy test will be carried out.

*Azathioprine*: at pre-baseline (week -4) TPMT activity will be measured, as described in paragraph 6.5. Furthermore, other laboratory tests are carried out, including: full blood count, ASAT, ALAT, ALP,  $\gamma$ -GT, bilirubine and serum creatinine. At week 1, 2, 4, 8, 12 and 24, these will be repeated.

Procedures extra for this study:

Patients will be given one week to consider participation. Due to this, one extra visit is needed to randomize the patient and obtain baseline data. A Patient Global Assessment (PaGA) one-item questionnaire will be obtained at week 12 and 24. This procedure is only extra in terms of obtaining a quantitative assessment of the qualitative report that a patient provides us in daily practice.

Patients will be asked to keep track of out-of-pocket costs on products for their hand eczema. During each visit, patients will be asked for direct and indirect medical and non-medical costs (see paragraph 8.1.2).

No diagnostic procedures or other treatments will be postponed for patients participating in this study. However, patients receive at least 1 week time to consider participation in the study.

Study overview:

In table 1 and 2 a systematic overview of the study for respectively the alitretinoin and azathioprine arm is presented.

**Table 1.** Study schedule – *alitretinoin* arm

| Visit                                                           | V-1
Screening | V0
Baseline Ali | V1 | V2 | V3 | V4 |
|-----------------------------------------------------------------|------------------|--------------------|----|----|----|----|
| Week                                                            | -1               | 0                  | 4  | 8  | 12 | 24 |
| Screening/baseline                                       |                  |                    |    |    |    |    |
| Check for clinical eligibility (inclusion/exclusion)            | x                |                    |    |    |    |    |
| Sign informed consent                                           |                  | x                  |    |    |    |    |
| Randomization                                                   |                  | x                  |    |    |    |    |
| Baseline data / demographics / medical history / baseline costs |                  | x                  |    |    |    |    |
| Laboratory exclusion criteria post randomization                |                  | x                  |    |    |    |    |
| Start medication                                                |                  | x                  |    |    |    |    |
| Treatment                                                |                  |                    |    |    |    |    |
| Escape medication assessment                                    |                  |                    | x  | x  | x  | x  |
| If applicable: dosage reduction assessment                      |                  |                    | x  | x  | x  | x  |
| Efficacy                                                 |                  |                    |    |    |    |    |
| Severity scoring
PGA / HECSI                                 |                  | x                  | x  | x  | x  | x  |
| Quality of life questionnaire
QOLHEQ                         |                  | x                  |    |    | x  | x  |

|                                                   |  |   |   |   |   |   |
|---------------------------------------------------|--|---|---|---|---|---|
| PaGA                                              |  |   |   |   | x | x |
| Costs                                      |  |   |   |   |   |   |
| Cost assessment                                   |  | x | x | x | x | x |
| Cost-utility questionnaire
EQ-5D-5L            |  | x |   |   | x | x |
| Safety                                     |  |   |   |   |   |   |
| Lab control                                       |  | x | x | x | x | x |
| Concomitant medication                            |  | x | x | x | x | x |
| Adverse events                                    |  |   | x | x | x | x |
| If applicable: premature
withdrawal assessment |  | x | x | x | x | x |

**Table 2.** Study schedule – *azathioprine* arm

| Visit                                                             | V-1
Screening | V0
Baseline Aza | V0a
Additional
Baseline Aza | L
A
B | L
A
B | V1 | V2 | V3 | V4 |
|-------------------------------------------------------------------|------------------|--------------------|-----------------------------------|-------------|-------------|----|----|----|----|
| Week                                                              | -5               | -4                 | 0                                 | 1           | 2           | 4  | 8  | 12 | 24 |
| Screening/baseline                                         |                  |                    |                                   |             |             |    |    |    |    |
| Check for clinical eligibility
(inclusion/exclusion)           | x                |                    |                                   |             |             |    |    |    |    |
| Sign informed consent                                             |                  | x                  |                                   |             |             |    |    |    |    |
| Randomization                                                     |                  | x                  |                                   |             |             |    |    |    |    |
| Baseline data/ demographics /
medical history / baseline costs |                  | x                  |                                   |             |             |    |    |    |    |
| TPMT assessment                                                   |                  | x                  |                                   |             |             |    |    |    |    |
| Laboratory exclusion criteria
post randomization               |                  |                    | x                                 |             |             |    |    |    |    |
| Dosage azathioprine baseline                                      |                  |                    | x                                 |             |             |    |    |    |    |
| Start medication                                                  |                  |                    | x                                 |             |             |    |    |    |    |
| Treatment                                                  |                  |                    |                                   |             |             |    |    |    |    |
| Escape medication assessment                                      |                  |                    |                                   |             |             | x  | x  | x  | x  |
| If applicable: dosage reduction
assessment                     |                  |                    |                                   |             |             | x  | x  | x  | x  |
| Efficacy                                                   |                  |                    |                                   |             |             |    |    |    |    |
| Severity scoring
PGA / HECSI                                   |                  |                    | x                                 |             |             | x  | x  | x  | x  |
| Quality of life questionnaire
QOLHEQ                           |                  |                    | x                                 |             |             |    |    | x  | x  |
| PaGA                                                              |                  |                    |                                   |             |             |    |    | x  | x  |
| Costs                                                      |                  |                    |                                   |             |             |    |    |    |    |
| Cost assessment                                                   |                  | x                  | x                                 |             |             | x  | x  | x  | x  |
| Cost-utility questionnaire
EQ-5D-5L                            |                  |                    | x                                 |             |             |    |    | x  | x  |
| Safety                                                     |                  |                    |                                   |             |             |    |    |    |    |
| Lab control                                                       |                  | x                  |                                   | x           | x           | x  | x  | x  | x  |
| Concomitant medication                                            |                  | x                  | x                                 |             |             | x  | x  | x  | x  |
| Adverse events                                                    |                  |                    | x                                 |             |             | x  | x  | x  | x  |
| If applicable: premature
withdrawal assessment                 |                  | x                  | x                                 |             |             | x  | x  | x  | x  |

Patients are permitted to deviate from the schedule with a maximum of 7 days during week 0-8. From week 9 a maximum deviation of 14 days is permitted.

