##### **8.4.1 Specific criteria for withdrawal**

- Evidence of pregnancy
- Occurrence of serious adverse events
- Lack of efficacy at 12 weeks, defined as no improvement assessed by the PGA (at least 1 step improvement is necessary to continue treatment after 12 weeks)
- Use of prohibited concomitant therapy, or a need for their use
- The need for more than 3 courses of rescue medication
- Anaphylactic reaction or other severe systemic reaction to study drug intake
- Diagnosis of malignancy during study, excluding non-metastatic cutaneous squamous cell or basal cell carcinoma and/or localized carcinoma in situ of the cervix
- Any infection that is opportunistic and other infections whose nature or course may suggest an immunocompromised status
- Administration of a living vaccine
- Severe laboratory abnormalities including:
  - ALAT and/or ASAT values > 300% of the upper limit of normal
  - Lowered full blood count indicating a possible (developing) myelosuppression (to be determined by investigator or treating physician)
  - Triglycerides > 9 mmol/l
- Intercurrent severe illness or major surgery
- Protocol violations or if the requirements of the protocol are not respected
- Patient lost to follow up

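### The 7-day deviation rule does not exempt azathioprine's week-1 and week-2 safety bloods, so the first on-treatment blood count may slip from day 7 to day 14

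*Protocol*

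**What the plan says.** Section 8.3 of the Protocol sets the azathioprine bloods (full blood count, liver tests, bilirubin, creatinine) at week -4 and then on treatment: "At week 1, 2, 4, 8, 12 and 24, these will be repeated". Table 2 shows weeks 1 and 2 as laboratory-only columns and places "Start medication" at week 0.

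The timing tolerance below Table 2 reads: "Patients are permitted to deviate from the schedule with a maximum of 7 days during week 0-8". From week 9 the allowance is 14 days. No item is exempted, and no separate window for blood samples is given. Section 8.3 does say that during therapy standard "monitoring of blood values is carried out, according to SPC texts and current guidelines", but it states no window there.

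Three other places bear on the point:

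- Section 6.4 lists myelosuppression, including severe forms, as a main azathioprine risk and adds that "this can occur independent of TPMT activity".
- Section 6.6 provides for a lower dose: "Dosage reduction is allowed in both groups in case of abnormal findings on physical examination, laboratory markers, and/or adverse events".
- Section 8.4.1 makes this a withdrawal criterion: "Lowered full blood count indicating a possible (developing) myelosuppression".

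**The concern.** A tolerance as long as the gap between two planned samples removes the guarantee that they are separate looks at the patient. Here those samples are the early on-treatment check for marrow and liver toxicity. In Table 2 no adverse-event, dose-reduction or withdrawal check is marked between week 0 and week 4, so the two draws are the only scheduled safety checks in that period. The table also marks no laboratory control at week 0, so the last count before treatment is the one at week -4.

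TPMT exclusion and TPMT-based dosing lower the risk but do not replace an on-treatment count, as the remark in section 6.4 makes plain. Laboratory-triggered dose reduction and withdrawal cannot act until there is a sample. Section 9.5 also relies on regular blood testing as one of its reasons for having no DSMB.

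For orientation only, section 13.1 (item j) puts the maximum of marrow suppression after an azathioprine overdose mostly at 9 to 19 days. That describes overdose, not the trial doses, but it shows that the timing of counts in the first weeks is not arbitrary.

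**Working it through.** **Inputs.** Day 0 is the first dose (Table 2, week 0). Planned draws are at weeks 1, 2 and 4 (section 8.3). The tolerance in weeks 0–8 is 7 days (below Table 2). The planned azathioprine arm is 58 of 116 patients (section 4.4). The protocol states no figure for the resulting windows, so there is none to reproduce beyond the planned days.

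**Planned timing.** Day = 7 × week: week 1 = day 7, week 2 = day 14, week 4 = day 28. Planned spacing of the first two draws: 14 − 7 = 7 days.

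**Current rule.** The text does not say whether deviation may be early as well as late, so both readings are shown.

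| | Both directions (±7) | Late only (+7) |
|---|---|---|
| Week-1 draw | 7 ± 7 = days 0–14 | days 7–14 |
| Week-2 draw | 14 ± 7 = days 7–21 | days 14–21 |
| Windows share | days 7–14 | day 14 |
| Latest week-1 draw | day 14 | day 14 |
| Smallest spacing | 0 days | 0 days |
| Largest spacing | 21 − 0 = 21 days | 21 − 7 = 14 days |

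The two results that matter, a first count as late as day 14 and a smallest spacing of 0 days, are the same under both readings.

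**Gap since the last pre-treatment count.** Week -4 is day −28. Planned gap to the first on-treatment count: 28 + 7 = 35 days. At the limit of the rule: 28 + 14 = 42 days.

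**Widest tolerance without overlap.** For draws 7 days apart and a tolerance of ±t, the windows stay separate if 7 + t < 14 − t, that is 2t < 7. In whole days, t ≤ 3. Spacing runs from 7 − 2t to 7 + 2t.

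| t | Week-1 window | Week-2 window | Latest first count | Spacing |
|---|---|---|---|---|
| 3 | days 4–10 | days 11–17 | day 10 | 1 to 13 days |
| 2 | days 5–9 | days 12–16 | day 9 | 3 to 11 days |

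**Check against week 4.** Week 4 is 28 ± 7 = days 21–35. Under the current rule read in both directions it touches the week-2 window on day 21. With t = 2 or t = 3 the week-2 window ends on day 16 or 17, so it no longer does.

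**The case against.** The strongest reply is that the sentence was meant for clinic visits. Table 2 numbers those as visits and labels weeks 1 and 2 only as laboratory columns, and section 8.1.2 refers to control visits at weeks 4, 8, 12 and 24. That reading is possible but weak. The rule speaks of the schedule, the table above it is titled a study schedule, and that table contains the two laboratory columns.

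A second reply is that section 8.3 already ties blood monitoring to the SPC and guidelines. Whether a first count on day 14 is clinically too late does depend on those sources, and that part stands. But the sentence prints no window, while the deviation rule gives an explicit permission. A patient first sampled on day 14 is within the protocol as written.

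Third, there are other safeguards: a pre-treatment blood count and liver tests, TPMT exclusion and dosing, an unblinded treating physician, and dose reduction on clinical findings as well as laboratory values. This stands and keeps the severity low.

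Fourth, same-day draws need an extreme pairing, and the tolerance waives neither draw. That is fair. The delay of the first count is the more realistic problem.

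Finally, ±3 days comes only from avoiding overlap and still allows draws 1 day apart. This is also correct, and it is why ±2 days is the better starting point and the team should settle the limit.

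**Conclusion.** The concern holds as a minor safety point. The rule as written permits a first on-treatment count on day 14 instead of day 7, and 0 days instead of 7 between the first two draws. The general rule covers both arms; the week-1 and week-2 problem arises only with azathioprine (58 of 116 planned patients).

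This rests on two assumptions: that the rule covers the laboratory columns, which is its plain reading, and that day 0 is the first dose. It does not depend on whether early deviation is allowed. The planned schedule itself is sound. The protocol neither shows that day 14 is unsafe nor says how often draws would run late, so no expected harm can be calculated. Endpoints, power and alpha are untouched.

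**What to change.** Add under Table 2, for example: *The week-1 and week-2 laboratory draws in the azathioprine arm are exempt from the general deviation. They are taken on days 5–9 and 12–16 after the first dose. A draw outside its window is taken as soon as possible and recorded as a timing deviation; it is not by itself a reason for withdrawal under section 8.4.1.*

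The team may choose another limit up to ±3 days and should check it against the SPC and guideline it already cites. The last clause is needed because section 8.4.1 lists as a withdrawal criterion: "Protocol violations or if the requirements of the protocol are not respected".

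The cost is two or three sentences, with no extra visits or samples. A few more timing deviations will be recorded. If the change is rated a substantial amendment under section 12.3, the METC and the competent authority must be notified.
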